### Outcomes

All outcomes will be collected online. Basic demographic data (age, gender, and academic level) will be collected at baseline (T0). Change in perceived stress, the primary outcome, will be assessed using the difference score of the stress scale of the German version of the DASS-21 [40], measured at baseline (T0) and at 1-week follow-up (T2). The stress scale of the DASS-21 consists of 7 items rated on a 4-point Likert scale (0 = “did not apply to me at all” to 3 = “applied to me very much or most of the time”), yielding total scores from 0 to 21 for the difference score. Higher difference scores indicate greater reduction in perceived stress.

The secondary outcomes are the change in depressive symptoms and anxiety. Change in depressive symptoms and anxiety will be assessed using the difference score of the respective DASS-21 scales, measured at T0 and T2. Each scale consists of seven items, which are rated on the same 4-point Likert scale as the stress scale (total difference score range: 0‐21). The additional exploratory outcome, self-compassion, will be measured using the short version of the German Self-Compassion Scale (SCS-D-KF) [41]. This scale comprises 12 items covering 6 dimensions of self-compassion. Each item is rated on a 5-point Likert scale (1=“almost never” to 5=“almost always”). The scale will be administered at T0, T1, and T2. The primary predictor variable is group allocation (intervention vs. waitlist control), which is assigned through randomization and coded dichotomously (0=control, 1=intervention). No data monitoring committee has been established due to the minimal-risk, single-session, fully automated nature of the intervention. Oversight will be provided by the principal investigators.

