### Statistical Methods

Analyses will follow a complete-case per-protocol (CC-PP) approach, including only participants who completed T0, T1, and T2 (complete cases). Inclusion and exclusion criteria for PP are prespecified in the protocol. Linear models in combination with type II ANOVA will be applied to investigate group differences for the primary and secondary outcomes.

The primary outcome is the change in perceived stress (DASS-21 stress scale) from baseline (T0) to 1-week follow-up (T2). Secondary outcomes are (1) change in depression (DASS-21 depression scale) from T0 to T2, and (2) change in anxiety (DASS-21 anxiety scale) from T0 to T2. Group allocation (intervention vs waitlist control) will be included as a between-subject factor.

For the additional outcome self-compassion (SCS-D-KF) (3), which is assessed at T0, T1, and T2, a linear mixed-effects model will be used, including visit (T1 and T2) as a within-subject factor and group as a between-subject factor. Subject ID will be included as a random effect to account for within-subject correlations across visits. Baseline self-compassion (T0) will be included as a covariate to adjust for individual differences at study entry.

Covariates (sex, age, and academic level) will be entered as main effects and as 2-way interactions with group. Nonsignificant interaction terms will be removed from the final model. If significant interactions are detected, post hoc tests will be conducted to explore and describe the effects.

Group differences in change scores of the Visual Analogue Scale stress from T0 to directly after the intervention will be analyzed as a manipulation check to assess whether the intervention produced the expected immediate effect on perceived stress.

Results will be reported as mean (SDs) for the intervention and control groups, 2-sided *P* values, and adjusted between-group differences with 95% CIs. For the secondary outcomes, the significance level will be adjusted using a Bonferroni correction for the number of independent tests. Effect sizes will be expressed as Cohen *d*, derived from the *t* values of the models and adjusted for covariates. By convention, *d*=0.2 will be interpreted as a small effect, *d*=0.5 as a medium effect, and *d*=0.8 as a large effect.

All analyses will be performed using R (version 4.5.X; R Development Core Team) [31].

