### Sample Size

We conducted an a priori power analysis for an independent-samples *t* test (2-tailed, *α*=.025, power=0.80, allocation ratio=1). The adjusted significance level reflects our decision to control for 2 independent tests corresponding to the 2 secondary hypotheses. Assuming a medium effect (Cohen *d*=0.5) for our primary outcome the change in perceived stress, the required total sample size was estimated as n=156 (78 per group; G*Power 3.1.9.6). Only participants who successfully pass screening will be counted toward the target sample size. Recruitment will be considered complete once 86 eligible participants per group have passed screening. Accordingly, 86 participants per group will be randomized. Assuming an expected attrition rate of 10% per group, we anticipate a final sample of 156 participants, with 78 participants in each group. Since SSIs are generally expected to yield effects in the small-to-medium range, with the strongest effects observed immediately after the intervention and up to 2 weeks later [26], a moderate effect size was deemed the most appropriate estimate.

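### Plain Bonferroni on the two secondary outcomes is valid, but Holm's step-down rule would give more power within the same 5% family-wise bound (optional improvement)

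*Protocol article*

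**What the plan says.** In the Protocol article, the Outcomes section defines the secondary family: "The secondary outcomes are the change in depressive symptoms and anxiety", each measured as the difference between baseline and 1-week follow-up on a DASS-21 scale. Self-compassion is labelled exploratory there and lies outside the family.

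Statistical Methods fixes the multiplicity rule: "For the secondary outcomes, the significance level will be adjusted using a Bonferroni correction for the number of independent tests". The Sample Size section gives the divisor: "The adjusted significance level reflects our decision to control for 2 independent tests corresponding to the 2 secondary hypotheses". The power calculation is run at that level ("2-tailed, *α*=.025, power=0.80, allocation ratio=1"). Since .025 = .05/2, the family-wise level is .05. No step-down or other sequential procedure is named.

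Results are to be reported as "2-sided *P* values, and adjusted between-group differences with 95% CIs", so the planned intervals are ordinary, not simultaneous, intervals.

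**The concern.** The article itself names the method, so this is not a detail left to an unseen analysis plan. Under plain Bonferroni, depression and anxiety are each held to .025 even after the other hypothesis has been rejected. At that point only one hypothesis is still open, and the family-wise budget would allow it to be tested at .05. Holm's procedure uses that allowance.

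Hypotheses 2 and 3 are stated separately in Research Objectives and Hypotheses, so confirming each one counts. With plain Bonferroni the trial will miss the second of two true effects more often than its own error budget requires.

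The plan also calls the two tests independent. Both are change scores from one questionnaire in the same participants, so the description is inaccurate.

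**Working it through.** **Inputs from the plan.** Two tests, two-sided, .025 each; 78 per arm ("the required total sample size was estimated as n=156 (78 per group; G*Power 3.1.9.6"); d=0.5, which the plan states for stress only ("Assuming a medium effect (Cohen *d*=0.5) for our primary outcome the change in perceived stress").

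**Inputs assumed here.** The plan gives no effect size for depression or anxiety and no correlation between the two test statistics. The check uses equal effects of d = 0.2 to 0.5 on both scales and correlations r = 0 to 0.8.

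**Step 1: reproduce the plan's figure.** Noncentral t, d=0.5, two-sided .025: 77 per arm gives power 0.798 and 78 per arm gives 0.804. The smallest adequate size is therefore 78 per arm, 156 in total, as stated. At 78 per arm and .05 the power is 0.873, so about 7 points separate the two levels for a single test.

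**Step 2: the two rules.** Bonferroni rejects each hypothesis if its P ≤ .025. Holm compares the smaller P with .025 and, only if that is rejected, the larger P with .05. Everything Bonferroni rejects, Holm rejects.

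**Step 3: closed form at r=0, d=0.5 (normal approximation).** The mean of each test statistic is d·√(n/2) = 0.5·√39 = 3.12. Power is 0.8109 at .025 and 0.8775 at .05.
- Both rejected, Bonferroni: 0.8109² = 0.658.
- Both rejected, Holm (both P ≤ .05 and at least one ≤ .025): 0.8775² − (0.8775 − 0.8109)² = 0.770 − 0.004 = 0.766.

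**Step 4: simulation over the assumed range.** 1,000,000 pairs of bivariate normal test statistics per scenario, 78 per arm. At r=0 it agrees with Step 3.

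| d on both scales | r | Both, Bonferroni | Both, Holm | Gain (points) | At least one (either rule) |
|---|---|---|---|---|---|
| 0.5 | 0 | 65.7% | 76.5% | 10.8 | 96.4% |
| 0.5 | 0.3 | 68.2% | 77.9% | 9.7 | 93.9% |
| 0.5 | 0.6 | 71.4% | 79.8% | 8.4 | 90.8% |
| 0.5 | 0.8 | 74.2% | 81.5% | 7.3 | 87.9% |
| 0.3 | 0 | 12.8% | 20.5% | 7.7 | 58.6% |
| 0.3 | 0.6 | 21.9% | 30.4% | 8.5 | 49.4% |
| 0.3 | 0.8 | 26.2% | 34.4% | 8.2 | 45.3% |
| 0.2 | 0 | 2.6% | 5.1% | 2.5 | 29.6% |
| 0.2 | 0.6 | 7.3% | 11.6% | 4.3 | 24.8% |
| 0.2 | 0.8 | 9.9% | 14.5% | 4.6 | 22.2% |

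Power per hypothesis rises from 81% to about 85–87% at d=0.5, from 36% to 40% at d=0.3, and from 16% to 17–18% at d=0.2.

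**Step 5: error.**
- Both nulls true: the rules make a family-wise error in exactly the same samples, 4.96% at r=0 (theory: 1 − 0.975² = 4.94%), 4.5% at r=0.6 and 4.1% at r=0.8.
- One null true, d=0.5 on the other scale: Bonferroni 2.5%; Holm 4.5% at r=0, falling to 3.9% at r=0.8. Closed form at r=0: .025 + .025 × 0.8109 = 4.5%.

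**The case against.** The strongest reply is that nothing here is wrong. Bonferroni on two secondary tests is valid, prespecified and conservative, and the two sections that mention it agree. A sponsor may also prefer a rule under which each test can be read without looking at the other. That stands: the case for change rests on efficiency alone.

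Four stronger readings are tempting, and the documents do not support them.
- **That the word independent invalidates the correction.** Bonferroni needs no independence, and the phrase serves only to give the divisor of two. It is a loose description. Conservatism under correlation also affects Holm's first step.
- **That Holm leaves the error rate unchanged.** Only the 5% bound is unchanged. With exactly one true null, the actual error rises, as Step 5 shows.
- **That d=0.5 on depression and anxiety is the plan's assumption.** It is stated for stress alone. The Sample Size section expects small-to-medium effects from such interventions. Recruitment and Eligibility Criteria excludes students scoring 10 or more on the depression scale at screening, which limits the room for that score to fall. The smaller-effect rows deserve equal weight.
- **That the trial becomes more likely to show some secondary benefit.** The chance of at least one rejection is identical under both rules. The gain falls only on the second hypothesis.

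Bonferroni's one practical advantage, simple matching simultaneous intervals, carries little weight here because the plan reports ordinary 95% intervals.

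**Conclusion.** The point holds as an optional efficiency improvement. For the decision on each secondary hypothesis, Holm never rejects less than plain Bonferroni and keeps the same .05 family-wise bound under any dependence. The gain in the chance of confirming both hypotheses is about 7 to 11 points at d=0.5, about 8 at d=0.3 and about 3 to 5 at d=0.2. These figures rest on 78 analysed per arm, equal effects on both scales and correlations of 0 to 0.8. The effect sizes and correlations are this review's assumptions, not the plan's.

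Against this stands a higher actual error when one null is true, about 4 to 4.5% instead of 2.5%, within the 5% the plan already allows. The primary test, the sample size of 156, the estimates and the intervals are untouched. It should not be read as a flaw that biases any result.

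**What to change.** Replace the Bonferroni sentence in Statistical Methods with wording such as: *The two secondary outcomes are tested with Holm's step-down procedure at a two-sided family-wise level of .05; the smaller P is compared with .025 and, only if it is significant, the larger with .05.* Leave the estimates and 95% intervals as planned. Drop the word independent in Statistical Methods and Sample Size and speak simply of two tests.

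No participants or data are needed, but the change is not free. Ethical Considerations sends protocol amendments to the ethics committee, and Trial Design says an analysis plan is already registered at two sites. A move to a more permissive rule during recruitment therefore needs a dated, justified amendment and registry updates before analysis. There is time: 67 of 172 participants were enrolled on April 15, 2026, no interim analysis is planned, and analysis is set for winter 2026.

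### Cohen d for self-compassion is derived from the mixed model's t value, so it is not in SD units of the scale, yet it gets the usual small, medium and large labels

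*Protocol article*

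**What the plan says.** All of the analysis text is in the Statistical Methods section of the protocol article.

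- Effect size: "Effect sizes will be expressed as Cohen *d*, derived from the *t* values of the models and adjusted for covariates". The conventional cut-offs of 0.2, 0.5 and 0.8 follow, with no distinction between outcomes. No conversion formula, df or standardiser is named.
- Stress, depression and anxiety: "Linear models in combination with type II ANOVA will be applied to investigate group differences for the primary and secondary outcomes". The outcome is the T0 to T2 change score, and no baseline score is named as a covariate.
- Self-compassion: "a linear mixed-effects model will be used, including visit (T1 and T2) as a within-subject factor and group as a between-subject factor", with a random subject effect. In addition, "Baseline self-compassion (T0) will be included as a covariate to adjust for individual differences at study entry".
- Further covariates: "Covariates (sex, age, and academic level) will be entered as main effects and as 2-way interactions with group".

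The Sample Size section plans for d = 0.5 on the change in stress, using an unadjusted two-sample t test. The Outcomes section calls self-compassion exploratory, but it is the fourth of the four stated hypotheses.

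**The concern.** The conventional cut-offs are meant for a mean difference divided by the between-person SD. A model t value is the adjusted difference divided by a standard error that contains only the variance left after adjustment. Turning that t back into d standardises by the reduced variance. The self-compassion model reduces it twice, by conditioning on T0 and by averaging two visits. For the same shift in SCS-D-KF points, a more precise model then gives a larger d and possibly a larger label.

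At stake is the size label attached to one of the four hypotheses, and any side-by-side reading of the self-compassion d and the DASS-21 d values. No test depends on it.

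**Working it through.** **Inputs from the article:** 78 analysed per group, d = 0.5, two-sided alpha 0.025, power 0.80 (Sample Size); the models as described in Statistical Methods.

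**Assumptions, not in the article:** equal SDs at all visits; the same correlation r between T0, T1 and T2, shown for 0.5 to 0.8; the same true shift at T1 and T2; conversion by d = 2t/√df.

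**1. The planning figure.** With the noncentral t distribution, power at d = 0.5 and alpha 0.025 is 0.798 with 77 per group and 0.804 with 78. The stated 78 per group (156 in total) reproduces. That d is in SD units of the change score.

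**2. What the conversion does.** With n per group, t = Δ/(s√(2/n)), where s is the SD on which the model's standard error rests. With df close to 2n, 2t/√df ≈ Δ/s. At n = 78 and df = 153 the approximation is off by √(156/153) = 1.01. So s is the implied standardiser.

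**3. The implied standardiser for self-compassion.** Take the variance of the scale at one visit as 1.

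- Two-visit group effect given T0: s² = (1+r)/2 − r². Inflation is 1/s.
- Single-visit contrast given T0: s² = 1 − r².
- Two-visit effect with observation-level df: df roughly doubles, so the first factor is divided by √2.

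| r | two-visit, between-subject df | single visit | two-visit, observation-level df |
|---|---|---|---|
| 0.5 | 1/√0.50 = 1.41 | 1/√0.75 = 1.15 | 1.00 |
| 0.6 | 1/√0.44 = 1.51 | 1/√0.64 = 1.25 | 1.07 |
| 0.7 | 1/√0.36 = 1.67 | 1/√0.51 = 1.40 | 1.18 |
| 0.8 | 1/√0.26 = 1.96 | 1/√0.36 = 1.67 | 1.39 |

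The first column never falls below 1.33 (at r = 0.25). If the correlation with T0 (0.5 to 0.8) and the T1 to T2 correlation (0.6 to 0.9) differ, it runs from 1.20 to 2.50. The last column can fall below 1 at lower correlations (0.945 at r = 0.3).

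**4. A true shift of 0.30 SD.** It would be reported as 0.30 × 1.41 = 0.42 to 0.30 × 1.96 = 0.59 in the first column, 0.35 to 0.50 in the second, and 0.30 to 0.42 in the third.

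**5. Check by simulation.** With 4000 trials per setting, 78 per group, a true shift of 0.30 and the two-visit effect with df = 153, the mean d was 0.43, 0.46, 0.50 and 0.60 for r = 0.5, 0.6, 0.7 and 0.8. The share of trials with d at or above 0.5 was 31%, 39%, 50% and 72%. Dividing the adjusted difference by the pooled T0 SD gave a mean of 0.30 throughout, and shares of 4%, 3%, 2% and 1%. Fitting the random-intercept mixed model itself in a smaller simulation (150 trials per setting) gave ratios of 1.42, 1.67 and 2.04 at r = 0.5, 0.7 and 0.8.

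**6. Stress, depression and anxiety.** Here s is the change-score SD after covariates. Relative to the unadjusted change-score SD, the factor is 1/√(1−R²), which is 1.01, 1.03 and 1.05 for R² of 2%, 5% and 10%. Relative to the SD of the scale itself, the change-score factor is 1/√(2(1−r)): 0.85 at r = 0.3, 1.00 at 0.5, 1.29 at 0.7 and 1.58 at 0.8. It can lie on either side of 1.

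**The case against.** The strongest reply has four parts.

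- **No fixed inflation.** A reader might take 1.4 to 2.0 as a property of the plan. The article does not support that, because it states no visit correlation, contrast or df. The self-compassion hypothesis names both post-baseline time points, so single-visit contrasts are plausible, and with observation-level df at r = 0.5 there is no inflation at all. This stands. It also shows that the rule as written permits d values differing by a factor of √2 from the same data through the df alone.
- **The primary outcome is safe.** A reader might infer that the stress d cannot be compared with the planned 0.5. The documents do not support this either: both are on the change-score scale and differ by about 1 to 5% for covariate R² of 2 to 10%. This stands in full.
- **Little depends on it.** Self-compassion is exploratory, and the covariate adjustment of d is disclosed. Group means with SDs and adjusted differences with CIs are promised, so a careful reader could rebuild a d in scale units. This lowers the weight, but a printed label is what gets quoted.
- **It is a detail for the analysis plan.** A registered plan exists and is not shown. But the article does not leave the matter open: it fixes the t-value route and the labels.

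It is also fair to say that baseline SD for one outcome and change-score SD for others still leaves two scales. That is why the standardiser must be named and cross-outcome comparison avoided.

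**Conclusion.** The point holds for self-compassion and is minor. The t-derived d is scaled by the SD of the two-visit mean given T0, or of a single visit given T0, rather than by the between-person SD of the SCS-D-KF. It would be loose to call that standardiser the model's residual error: in a mixed model it combines the subject variance with half the residual variance, and the residual SD alone would give 1.41 to 2.24.

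The size is conditional on the correlation, contrast and df set out above. It is also too strong to say that a small effect will be reported as medium. Even under the two-visit reading, a 0.30 SD shift averages below 0.5 at r = 0.5 and 0.6; it may cross the mark, no more. Sample size, tests, P values and CIs of the adjusted differences are untouched.

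**What to change.** Replace the effect-size sentence in Statistical Methods with a rule that does the following:

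- For self-compassion, compute d as the covariate-adjusted mean difference at each visit divided by the pooled T0 SD of the SCS-D-KF, with a 95% CI. Apply the small, medium and large labels for this outcome only to that d.
- For stress, depression and anxiety, divide the adjusted difference by the unadjusted pooled SD of the change score, the scale of the planned d = 0.5.
- Name the standardiser beside each d, and do not compare d across outcomes that use different ones.

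The cost is a short change of text and a few lines of R. Analysis is planned for winter 2026, so it can be settled beforehand. The one drawback is that the reported self-compassion d will probably be smaller.

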### Attrition and Assessment of Potential Bias Under the CC-PP Approach

As the primary analyses follow a CC-PP approach requiring observed data at T0, T1, and T2, potential bias due to attrition will be assessed. Completion rates will be summarized by randomized group and compared using chi-square or Fisher exact tests, as appropriate. Baseline characteristics will be compared between completers and noncompleters, prioritizing the corresponding T0 value of each primary and secondary outcome, using appropriate statistical tests and standardized mean differences.

To formally evaluate differential attrition while accounting for baseline outcome severity, dropout will be modeled separately for each outcome using logistic regression with treatment group as the primary predictor, adjusted for the respective outcome’s T0 value as well as age and sex (dropout ~ group+outcome_T0+ age+sex). If the number of dropout events is insufficient to support covariate-adjusted models, parsimonious models will be fitted as prespecified. Sensitivity analyses under an intention-to-treat framework using linear mixed-effects models with all available repeated measures will be conducted to assess the robustness of the per-protocol findings to different assumptions about missing data.

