## Methods

### Trial Design

This design is a randomized, controlled, parallel-group trial with 2 arms (intervention vs waitlist control) (Figure 1). No additional interventions will be provided beyond the intervention itself during the research period. Assessments will be carried out at baseline (T0), 24 hours after the intervention (T1), and at 1-week follow-up (T2). The trial protocol has been registered at the Open Science Framework [27] and the German Clinical Trial Register (Identifying number DRKS00038409), including prespecified outcomes and a statistical analysis plan (Figure 1).

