### Randomization and Blinding

Prior to recruitment, a computer-generated randomization sequence will be created using R [31,30] with a 1:1 allocation to the intervention group and waitlist control group. Simple randomization without blocking or stratification will be used. Participants will be added sequentially to the pregenerated randomization sequence by the personnel responsible for enrollment. For procedural reasons, participants will be randomized before all inclusion and exclusion criteria have been fully verified, as group-specific access links must be provided immediately after successful screening. In the event of a screening failure, the next eligible participant will replace the excluded individual. Once enrolled, the intervention and all subsequent outcome assessments will be made available automatically on the study platform. Automated email reminders to fill in outcome assessments at T1 and T2 will be programmed at enrollment. Investigators do not interact with participants regarding allocation. The personnel enrolling participants have access to the randomization list solely for the purpose of sequentially adding participants. They do not have any influence over assignment beyond adding participants to the list. After a participant is added, allocation, intervention delivery, and outcome assessments are fully automated, preventing any post-enrollment influence by investigators. Participants are not explicitly informed of their group assignment, although they may infer it from the information provided during the informed consent process. As the intervention and outcome assessments are fully automated, no blinding of investigators is required. The data analyst responsible for statistical analyses will remain blinded to group allocation, with group labels coded to ensure that the data analyst is unaware of which condition corresponds to the intervention or waitlist control group during data analysis.

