### Adherence, Retention, and Discontinuation

Access to the intervention will be provided to participants in the intervention group directly after enrollment in the trial. Participants in the waitlist control group will receive access to the intervention after the completion of the final follow-up assessment (T2). No additional measures will be implemented to enhance adherence due to the single-session, automated, and self-guided nature of the SSI, and no ongoing investigator involvement will be required.

Several strategies will be used to promote participant retention. First, the overall time burden of the intervention and outcome assessments is less than an hour. Second, the follow-up intervals are short, with assessments conducted 24 hours and 7 days after the intervention. Third, participants will receive automated reminders to complete the outcome assessments at each follow-up assessment. Finally, participants will be offered the opportunity to enter a raffle as compensation for their participation.

Participants may withdraw from the trial at any time without consequences. No further data will be collected from participants after withdrawal. No investigator-initiated withdrawal will occur unless participants actively request withdrawal. Participants who discontinue the intervention or request withdrawal will be classified as dropouts, as the intervention cannot be adapted, modified, or resumed once discontinued. Loss to follow-up at each assessment time point, including T2, will be recorded.

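### The primary complete-case set requires the 24-hour questionnaire (T1), although the stress, depression and anxiety outcomes use only T0 and T2

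*Protocol article*

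**What the plan says.** The Statistical Methods section sets a complete-case per-protocol approach, "including only participants who completed T0, T1, and T2 (complete cases". The section on attrition under that approach repeats the condition for the main comparison: "As the primary analyses follow a CC-PP approach requiring observed data at T0, T1, and T2".

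The outcomes need less than this. In Statistical Methods, "The primary outcome is the change in perceived stress (DASS-21 stress scale) from baseline (T0) to 1-week follow-up (T2". In Outcomes, depression and anxiety are each the "difference score of the respective DASS-21 scales, measured at T0 and T2". The linear models for these three outcomes contain group, sex, age and academic level, and no T1 value.

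The one analyzed outcome stated to use T1 is self-compassion, which Outcomes labels exploratory: "The scale will be administered at T0, T1, and T2". Its mixed model takes T1 and T2 as the repeated visits, T0 as a covariate and subject as a random effect.

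The attrition section also plans completion rates by arm, a comparison of completers with noncompleters, a logistic model for dropout, and a sensitivity analysis under intention to treat with a mixed model on all available measures.

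**The concern.** A rule for complete cases should ask for the data that the analysis uses. Here it asks for one visit more. Someone who fills in T0 and T2 but not T1 has an observed change in stress and is still excluded from the primary result.

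Two things are at stake. One is precision: observed primary outcomes are set aside, and no DASS-21 model gains from it. The other is comparability. Answering T1 happens after randomization, and T1 falls 24 hours after a session that the waitlist arm has not yet had, so response at T1 could plausibly differ by arm. Conditioning on it opens a route for selection that the outcome definition does not require.

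The rule also blurs the attrition model. That model is to be fitted separately for each outcome, yet under a three-visit rule the same people are noncompleters for every outcome, including some whose DASS-21 change is observed.

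**Working it through.** **Can the case arise?** Yes.
- Trial Design lists T1 and T2 as separate assessments: "Assessments will be carried out at baseline (T0), 24 hours after the intervention (T1), and at 1-week follow-up (T2".
- Nothing makes T2 depend on T1: "Automated email reminders to fill in outcome assessments at T1 and T2 will be programmed at enrollment".
- A missed T1 form is not among the listed grounds for being a dropout: "Participants who discontinue the intervention or request withdrawal will be classified as dropouts".
- The built-in completeness checks (Ethical Considerations) prevent skipped items within a submitted form. They cannot prevent a form that is never submitted.

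**Inputs (Sample Size section).** Cohen d = 0.5; two-sided alpha .025; power 0.80; ratio 1:1; 86 randomized per group; 10% attrition per group. *Assumed, not in the article:* m, the share of T2 responders who missed T1.

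**The plan's own figure.** With n per group, the noncentrality is d × √(n/2) and the degrees of freedom are 2n − 2. For n = 78 the noncentrality is 0.5 × √39 = 3.122 with 154 degrees of freedom, and power is 0.804. For n = 77 power is 0.798. So 78 per group (156 in total) reproduces. After attrition, 86 × 0.90 = 77.4 per group (154.8 in total), with power 0.801.

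**Reading A: the 10% is loss at T2 only, and missed T1 comes on top.** The analyzed number per group is 77.4 × (1 − m), and the observed outcomes set aside are 154.8 × m.

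| m | n per group | outcomes set aside | power |
|---|---|---|---|
| 0 | 77.4 | 0 | 0.801 |
| 1% | 76.6 | 1.5 | 0.796 |
| 2% | 75.9 | 3.1 | 0.792 |
| 5% | 73.5 | 7.7 | 0.778 |
| 10% | 69.7 | 15.5 | 0.753 |

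**Reading B: the 10% already includes missed T1.** The three-visit set is then 77.4 per group, and power stays at about 0.80. The set with T0 and T2 is larger, at 77.4 / (1 − m). With m = 5% this is 77.4 / 0.95 = 81.5 per group and power of about 0.822. The rule then costs about 2 × (81.5 − 77.4) = 8 observed outcomes, but the planned power is kept.

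**Which reading fits better?** Sample Size ties the 10% to a final sample of 156, and Results calls that target completed cases. Statistical Methods defines complete cases by all three visits. Reading B is the more natural one, although the article does not say so outright.

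**The case against.** The strongest reply is that the planned size already allows for the rule. On Reading B the trial keeps its 0.80, and the condition only forgoes a gain. That stands. A reader might infer from Reading A that the T1 rule leaves the trial underpowered. The article does not support this: it gives no rate of missed T1 and one undivided attrition figure, and with a one-week schedule and reminders the share could be small.

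A reader might also infer that the problem remains if the sponsor moves to intention to treat. It does not. The planned mixed model uses all available measures, so a missed T1 excludes nobody there. The point belongs to the complete-case set alone. Nor would selection go unwatched, since completion by arm, baseline differences and differential dropout are all to be examined. These checks can show a problem, but they do not put the excluded people back into the primary estimate.

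A single common set has some merit: all four hypotheses would then be tested on the same people, and self-compassion is the fourth. It is a recognizable choice, but it makes the primary outcome pay for an exploratory one, whose mixed model can itself use a person with one follow-up visit missing.

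Finally, the registered analysis plan and Figure 1 are not shown, so it is unknown whether the DASS-21 is also given at T1. This does not change the point. The article states the T1 condition twice, and its primary and secondary outcomes use T0 and T2 in any event.

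**Conclusion.** The point holds as a badly fixed analysis set. As written, the primary result leaves out participants whose primary outcome is observed, because of a visit that the primary and secondary models do not use. The logic rests on the article's own definitions and needs no assumption about rates.

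The size does need one. With 1% to 10% of T2 responders missing T1, the cost is between 0.005 and 0.048 of power below 0.801 if the attrition allowance covers T2 only. If the allowance already covers missed T1, the cost is a forgone gain, about 0.02 at 5%. Differential selection by arm is possible, but nothing in the article shows that it occurs. The planned sensitivity analysis is a partial safeguard, because the headline estimate would still exclude these participants.

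**What to change.** 1. Define the analyzed set per outcome. The DASS-21 models use everyone with T0 and T2. The self-compassion mixed model uses everyone with T0 and at least one of T1 or T2.
2. Delete T1 from the complete-case condition for the DASS-21 outcomes, both in Statistical Methods and in the attrition section.
3. In the attrition model, define noncompletion per outcome: missing T2 for stress, depression and anxiety; missing both T1 and T2 for self-compassion. Otherwise someone with T0 and T1 only would be both analyzed and counted as lost. Keep this term distinct from the dropout classification in the section on adherence, retention and discontinuation.
4. State which definition of completed cases the target of 156 in Results uses. That target ends data collection, so it should not shift unnoticed. It can be left as it is.

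The change uses data already being collected. It needs edits in the sections named and the usual amendment, with 67 participants enrolled as of April 15, 2026 and analysis not begun. The one small downside is that the analyzed sets differ slightly between outcomes, so each result should report its own number.
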